### Self-report physical activity

Incidental and planned exercise questionnaire (IPEQ): The IPEQ is a self-report questionnaire for assessing low, basic and high-intensity physical activities. It is suitable for use in ageing research including falls prevention trials. The IPEQ covers the frequency and duration of planned activities and incidental physical activities in older adults. A total activity score is obtained by multiplying frequency scores and duration scores. The IPEQ can discriminate between physical activity levels across groups that differ by fall risk factors. It has been shown to have strong test-retest reliability, validity, and internal consistency (
Delbaere *et al.*, 2010).

### Loneliness

University of California Los Angeles (UCLA) Loneliness Scale: In line with the
*Irish LongituDinal Study on Ageing* (TILDA), we will measure loneliness using a modified version of the UCLA Loneliness scale (
Russell, 1996). This version consists of five items: 1) How often do you feel you lack companionship? 2) How often do you feel left out? 3) How often do you feel isolated from others? 4) How often do you feel in tune with the people around you? 5) How often do you feel lonely? Each question has three response options (hardly ever or never = 0, some of the time = 1, often = 2). Responses to the five items were summed, resulting in an overall score ranging from 0 (not lonely) to 10 (extremely lonely). This scale will provide a self-report measure of emotional loneliness and thus the individual’s subjective satisfaction with the quality of their social relationships, which is considered the psychological embodiment of social isolation.

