Table 1.

**Table 1. T1:** Summary of the key study objectives, outcomes and analysis plans.

Aim	Objectives	Outcome	Criterion for Feasibility	Statistical Analysis
**Primary**	Assess feasibility of recruitment, retention, group size and data completion.	Recruitment and retention rates, missing data.	*Music and Movement for Health* is feasible. The rate of participants recruited to the study, retention rate (the number of participants who complete measures at baseline and at follow up post intervention, minimum average attendance (number of participants who attended at least 65% of the intervention sessions). We will calculate the minimum outcome assessment target, as a retention rate of at least 80% of recruited participants with valid baseline and 12-week primary outcome data.	To assess if we can recruit and retain sufficient eligible older adults to inform a future definitive trial. Descriptive statistics: mean and SD for continuous variables proportions for dichotomous variables.
	Assess safety of the programme.	Safety: adverse effects e.g., falls, a weekly falls log will be completed.	The programme is safe. There is no increase in direct adverse events due to the intervention (e.g., falls during the intervention period).	Safety assessed through self-report of direct or unrelated adverse events (e.g., falls or pain during the programme period).
	To obtain participants’ & stakeholder feedback and experiences of the study processes and programme.	Qualitative study feedback.	*Music and Movement for Health* is acceptable. The majority of participants report that the study processes including measures were feasible and acceptable.	Thematic analysis. Data regarding combined completion and acceptability of measures.
	Objective	Outcomes	*Hypothesis*	Statistical Analysis
**Secondary**	To explore the differences between the groups for Physical Function, Balance, Physical Activity, Loneliness, Social Isolation, Mood, and Quality of Life.	Results for Clinical outcomes: Physical Function, Balance, Physical Activity, Loneliness, Social Isolation, Mood, and Quality of Life.	The programme group will show improvement in scales.	Regression analysis

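### The loneliness score codes a positively worded item in the same direction as the four negative ones, so the stated coding cannot produce the stated 0 and 10 anchors

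*Protocol article*

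**What the plan says.** The Loneliness section of the protocol article adopts a modified, five-item UCLA scale, in line with the national longitudinal study on ageing. Four items ask about negative states: lacking companionship ("1) How often do you feel you lack companionship"), being left out, being isolated and feeling lonely. The remaining one asks about a positive state: "4) How often do you feel in tune with the people around you".

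One coding is given for all five: "Each question has three response options (hardly ever or never = 0, some of the time = 1, often = 2". The total is then defined: "Responses to the five items were summed, resulting in an overall score ranging from 0 (not lonely) to 10 (extremely lonely".

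Table 1 lists loneliness among the secondary outcomes. The objective is "To explore the differences between the groups for Physical Function, Balance, Physical Activity, Loneliness, Social Isolation, Mood, and Quality of Life", by regression, with the hypothesis "The programme group will show improvement in scales". A further row of Table 1 uses the results for these outcomes, through the ICC and the design effect, to size a definitive trial.

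**The concern.** For items 1, 2, 3 and 5, a frequent answer means a lonelier person. For item 4 it means a better connected one. A total that runs from not lonely to extremely lonely needs item 4 turned round before it is added. The section specifies the same codes for each question and a plain sum, and no other part of the article mentions reversal. The coding rule and the meaning given to the end points therefore cannot both be right.

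At stake is the preliminary estimate for one of the secondary outcomes, together with the SD and ICC that would pass to the definitive trial. The programme is meant to build social connection, so item 4 could plausibly respond to it. Under the written rule, a gain on that item would be recorded as more loneliness.

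**Working it through.** **Inputs from the Loneliness section.** Five items; codes 0, 1 and 2 with often = 2 on each; total = plain sum; anchors 0 = not lonely and 10 = extremely lonely; item 4 positive, the other four negative.

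**Step 1: the stated range.** Minimum 5 × 0 = 0 and maximum 5 × 2 = 10. The numerical range reproduces.

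**Step 2: the stated anchors.** Item order is 1 to 5; reversal replaces item 4's code x4 by 2 − x4.

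| Response pattern | Meaning | Sum as written | Item 4 reversed |
|---|---|---|---|
| 0, 0, 0, 2, 0 | least lonely | 2 | 0 |
| 2, 2, 2, 0, 2 | loneliest | 8 | 10 |
| 0, 0, 0, 0, 0 | no negative feelings, but hardly ever in tune | 0 | 2 |
| 2, 2, 2, 2, 2 | all negative feelings, but often in tune | 10 | 8 |

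The anchors hold only with item 4 reversed. With S the sum of the other four items, the error per person is (S + x4) − (S + 2 − x4) = 2(x4 − 1). That is −2, 0 or +2 points, depending only on the answer to item 4.

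**Step 3: raw between-group difference.** Let the programme lower the sum of the four negative items by D and improve item 4 by t, both towards less loneliness. The correctly keyed difference is D + t; the difference as written is D − t.

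- Equal shift d on every item: D = 4d and t = d, so 3d as written against 5d. The ratio is 0.60, a loss of 40%.
- Item 4 does not move: t = 0, so both give D and the raw difference is unchanged.
- Sign reversal requires t > D: item 4 alone must shift by more than the other four combined.

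**Step 4: SD and standardised effect.** The article gives no item correlations. Assume unit-variance items with a common correlation ρ once all point the same way. Of the 10 item pairs, 4 involve item 4 and change sign in the plain sum.

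- Variance, correctly keyed: 5 + 2 × 10ρ = 5 + 20ρ.
- Variance as written: 5 + 2 × (6 − 4)ρ = 5 + 4ρ.
- Standardised ratio under equal shifts: 0.60 ÷ (SD as written ÷ SD correctly keyed).

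| ρ (assumed) | SD correctly keyed | SD as written | SD ratio | Standardised ratio, equal shifts | Loss |
|---|---|---|---|---|---|
| 0.2 | √9.0 = 3.00 | √5.8 = 2.41 | 0.80 | 0.747 | 25% |
| 0.4 | √13.0 = 3.61 | √6.6 = 2.57 | 0.71 | 0.842 | 16% |
| 0.6 | √17.0 = 4.12 | √7.4 = 2.72 | 0.66 | 0.909 | 9% |

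The SD is understated by about 20% to 34% under these assumptions. This is why the standardised loss is smaller than the raw loss. If item 4 does not move, the same smaller SD makes the standardised effect look larger, by 3.00 ÷ 2.41 = 1.25 times at ρ = 0.2 and 4.12 ÷ 2.72 = 1.52 times at ρ = 0.6. The direction and size of the change in the ICC cannot be worked out from the article.

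**Step 5: what does not change.** The precision figures in the Sample size section concern recruitment, retention and attendance proportions. No loneliness quantity enters them.

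**The case against.** The strongest reply is that the trial may well score the scale correctly. The section follows an established national study and a published instrument, and its anchors make sense only with item 4 reversed. Its past tense could suggest a description carried over from elsewhere with the reversal step lost. Scoring syntax is also commonly left to the full protocol or analysis plan.

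Part of this stands. A reader might infer that the trial will certainly report a mis-keyed score; the article does not show that, because neither the database derivation nor the analysis syntax is visible. But the article is not silent on scoring. It gives the codes, applies them to each question, gives the summation and gives the anchors, and these conflict. A reference to another study does not override an explicit coding rule.

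The reply is right about size. A reader might infer that the written rule cancels part of any programme effect, or that the sign is likely to flip. The first holds only if item 4 itself moves. The second needs item 4's shift to exceed that of the other four items together, and nothing in the article suggests it would. The 40% figure is a raw-scale illustration under equal shifts, not a prediction. Loneliness is also one of several unranked secondary outcomes, and the Data analysis section puts the emphasis on description and confidence intervals.

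**Conclusion.** The point holds as an internal contradiction: the coding and plain sum in the Loneliness section cannot yield that section's own anchors. This rests on the item wording and simple arithmetic, with no outside source. Followed literally, the rule puts each person's total wrong by −2, 0 or +2 points on a 10-point scale and distorts the preliminary estimate, its SD and its ICC.

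The effect on the group comparison depends on how item 4 responds, as Steps 3 and 4 show. The 40% raw loss and the 9% to 25% standardised loss rest on equal item shifts. The standardised range also rests on equal item variances and an assumed common correlation of 0.2 to 0.6.

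Severity is moderate. It would be too strong to read this as a threat to the trial's main purpose: recruitment, retention, attendance and the target of 72 participants do not depend on this score. Nor does the article single out loneliness as the outcome that will size the definitive trial.

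**What to change.** In the Loneliness section, state that item 4 is reverse-coded before summing (hardly ever or never = 2, some of the time = 1, often = 0), while the other four items keep the stated codes. The 0 and 10 anchors then hold as they stand.

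Check that the derivation in the electronic database and the analysis syntax apply the reversal. Two test records are enough: the least lonely pattern must return 0 and the loneliest must return 10.

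The cost is one sentence and, if the reversal is not already programmed, one line of code. Provided item-level responses are kept, the correction also applies to data already collected, with no change to the questionnaire or assessments.

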### Social Isolation

Berkman-Syme Social Network Index (SNI): Again in line with TILDA, we will measure social isolation using the Berkman-Syme SNI (
Berkman & Syme, 1979). This index categorises individuals into four levels of social connection using a 0–4 composite scale, whereby, socially isolated is scored at 0-1; moderately isolated at 2; moderately integrated at 3; and socially integrated at 4. The four types of social connections are: (1) marital status; (2) sociability (number and frequency of contacts with children, relatives and friends); (3) active church group membership; and; (4) membership in other community organisations.

### Cognition

The Trail Making Test (TMT) is used to measure cognitive functioning. The TMT involves attention, visual screening ability, processing speed, mental flexibility, and executive functions. Part A of the TMT requires an individual to draw a continuous line to connect 25 encircled numbers that are randomly distributed on a page. Part B of the TMT requires individuals to connect 24 circles with numbers and letters, switching between numbers and letters in consecutive order. The score on each part represents the amount of time required to complete the task. The TMT has shown to be a reliable and valid outcome measure in healthy older adults (
Cangoz *et al.*, 2009).

### Quality of Life and wellbeing and mood

The EQ-5D-5L measures quality of life using a scale from 1 to 5 across five domains (mobility, self-care, usual activities, pain, and anxiety/depression) and a visual analogue scale from 0 to 100 to determine subjective physical health. Compared to the EQ-5D-3L, research demonstrates that the EQ-5D-5L has a reduced ceiling effect and increased reliability as well as an improved ability to discriminate between different levels of health (
Janssen *et al.*, 2013).ICEpop CAPability measure for Older people (ICECAP-O): ICECAP-O was developed for use in the economic evaluation of health and social care programmes. It measures wellbeing based on an individual’s capability to ‘do’ and ‘be’ the things that are important to them. ICECAP-O covers five domains that were found to be important to older people: attachment, security, role, enjoyment and control (
van Leeuwen *et al.*, 2015).The 5-item Geriatric Depression Scale (GDS-5) will be used to measure mood. The GDS-5 was chosen to evaluate the effect of the music and movement programme on the mood of the participants. GDS-5 is a tool for measuring depression in older adults. The short version GDS-5 has sufficient sensitivity (97%) and good reliability. The questionnaire is composed of fives items to which it is necessary to answer ‘yes’ or ‘no’. This form can be completed in approximately 1 to 3 minutes (
Hoyl *et al.*, 1999).

A pilot health economic analysis will be conducted in conjunction with the feasibility trial. The health economic evaluation will evaluate the costs and outcomes of the programme jointly so as to understand the economic effectiveness of the
*Music and Movement for Health* programme. For the cost-utility analysis, Quality Adjusted Life-Years (QALYs) will be estimated using data collected via the EQ-5D-5L survey instrument at baseline and over the follow-up period. Missing data will be analysed to explore the validity of the data collection tools and the timing of their application. An incremental analysis will be conducted to calculate the mean differential in costs and QALYs between the control group and the programme group. The incremental cost-effectiveness ratio (ICER) will be calculated and analysed. Parametric and probabilistic analyses will be employed to explore uncertainty. The evidence generated from the pilot study will go to inform the design and conduct of a full economic evaluation to assess the cost-effectiveness of the developed programme.

### Process evaluation

*Music and Movement for Health* will include a mixed-methods process evaluation. For the quantitative process evaluation, personnel delivering the programme and participants will maintain session attendance logs for each session to measure protocol adherence, reason for non-attendance, retention and programme fidelity (proportion of key programme components [exercise prescription] provided and level of engagement). To assess the suitability of the eligibility criteria and success of the recruitment strategies, we will evaluate if referred participants represent our target population, the reasons for refusal, success of the various recruitment strategies and if sufficient recruitment rates were achieved. For the qualitative process evaluation, stakeholders and participants will be invited to participate in either semi-structured interviews or focus groups. We aim to have one focus group per cluster, however participants will be free to decide if they would like to participate and will be aware that participation in this component is entirely voluntary. Participants can choose to contribute to this part of the study or not and either in a focus group or an individual interview depending on their availability and preference. The information sheet will detail the option of participating in a focus group or individual interview. In the process evaluation we will explore participant expectations, views and beliefs on the study including acceptability of the study processes, their opinions and experiences of the programme and any facilitators and barriers to participation. Research recommends a combination of interviews and focus groups as it is pragmatic and can enrich the data. The focus groups will facilitate development and discussion of a variety of views and ideas through participant interaction in a comfortable, safe and supportive environment. The interviews will enable an in-depth understanding of the individual's experience and enables the exploration of personal perspectives and interconnectivity in personal perspectives. The focus groups and interviews will be arranged for a convenient time and location and will be audio-recorded and transcribed verbatim. Similarly, a qualitative evaluation of the programme will be conducted with the people involved in recruitment, referral and delivery of the programme. We will explore their views on the study including facilitators and barriers to upscaling to a full programme. A summary of the study’s key objectives can be found in
Table 1.

**Table 1. T1:** Summary of the key study objectives, outcomes and analysis plans.

Aim	Objectives	Outcome	Criterion for Feasibility	Statistical Analysis
**Primary**	Assess feasibility of recruitment, retention, group size and data completion.	Recruitment and retention rates, missing data.	*Music and Movement for Health* is feasible. The rate of participants recruited to the study, retention rate (the number of participants who complete measures at baseline and at follow up post intervention, minimum average attendance (number of participants who attended at least 65% of the intervention sessions). We will calculate the minimum outcome assessment target, as a retention rate of at least 80% of recruited participants with valid baseline and 12-week primary outcome data.	To assess if we can recruit and retain sufficient eligible older adults to inform a future definitive trial. Descriptive statistics: mean and SD for continuous variables proportions for dichotomous variables.
	Assess safety of the programme.	Safety: adverse effects e.g., falls, a weekly falls log will be completed.	The programme is safe. There is no increase in direct adverse events due to the intervention (e.g., falls during the intervention period).	Safety assessed through self-report of direct or unrelated adverse events (e.g., falls or pain during the programme period).
	To obtain participants’ & stakeholder feedback and experiences of the study processes and programme.	Qualitative study feedback.	*Music and Movement for Health* is acceptable. The majority of participants report that the study processes including measures were feasible and acceptable.	Thematic analysis. Data regarding combined completion and acceptability of measures.
	Objective	Outcomes	*Hypothesis*	Statistical Analysis
**Secondary**	To explore the differences between the groups for Physical Function, Balance, Physical Activity, Loneliness, Social Isolation, Mood, and Quality of Life.	Results for Clinical outcomes: Physical Function, Balance, Physical Activity, Loneliness, Social Isolation, Mood, and Quality of Life.	The programme group will show improvement in scales.	Regression analysis
	To explore the differences between the groups for Physical Function, Balance, Physical Activity, Loneliness, Social Isolation, Mood, and Quality of Life.	Results for each outcome of interest.	We can determine the required sample size for a definitive trial.	ICC (intraclass correlation coefficient) will be used to calculate the design effect. Thus, the required sample size for a CRCT (cluster-randomised controlled trail) will be calculated by multiplying the required sample size for the equivalent ungrouped study with the DE.
	Pilot economic analysis to assess costs and inform a definitive trial.	A pilot economic analysis to inform the design and conduct of a full economic evaluation to assess the cost effectiveness of the programme developed.	The methods developed and implemented for the conduct of the pilot health economic analysis proved to be feasible and acceptable to study participants.	The criterion for success includes obtaining sufficient data on cost. Incremental analysis to calculate the mean differential in costs and QALYs. The incremental cost effectiveness ratio (ICER) will be calculated and analysed. Parametric and probabilistic analyses will be employed to explore uncertainty.

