## Abstract

**Background:** Arts-based health programmes (ABHP) can enhance the physical and psychosocial health and wellbeing of older people. However, the feasibility and usefulness of such programmes in Ireland are currently unknown. The primary aim of this study is to examine the feasibility of the study design, its application to a music and movement for health programme and associated costs. The secondary aim is to obtain preliminary effect estimates of an ABHP on health and wellbeing in older adults.

**Methods:** This study is a pragmatic cluster-randomised controlled feasibility trial. Community-dwelling adults, aged 65 years or older will be recruited in the mid-west region of Ireland via methods including social prescription, traditional and social media. The clusters, based on geographical region, will be block randomised to either the ABHP or control using 1:1 allocation ratio. The programme will comprise a 1.5-hour music and dance session each week for 12-weeks together with a 1-hour home-based music and movement programme for 12-weeks. A qualitative and quantitative process evaluation of the arts-based health programme will be performed.

**Outcomes:** Primary outcomes for feasibility include recruitment rates (the number of participants recruited per cluster per month); retention rate (the number of participants who complete measures at baseline and at follow up post intervention, and minimum average attendance. Secondary outcomes will include physical function, balance, physical activity, loneliness, social isolation, cognition, mood, as well as quality of life and cost.

**Conclusions:** If this pioneering study finds evidence to support feasibility and acceptability, a future larger-scale definitive trial will be conducted to examine the effectiveness of an arts-based health programme for older adults. This research aims to strengthen collaborative efforts to implement effective, sustainable and cost-effective programmes for older adults to support community connection, enhancing health and wellbeing, in turn reducing demands on the healthcare system.

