### Sample size

As our primary outcomes are feasibility it is desirable to keep the sample size small enough to allow close monitoring of participants and the programme while large enough to obtain sufficient data on our primary outcomes of feasibility. For feasibility reasons we will ensure we have sufficient numbers in each group to generate a ‘group’ climate likely to maximise adherence. Hence if the group gets too small, it becomes unviable for participant engagement and sense of community. The minimum numbers required to sustain a community-based music and movement programme and maintain the required group dynamics is between 10–12 older adults per group; guided by practice expertise within the research team and previous feasibility studies (
Clifford *et al.*, 2021;
O’Regan *et al.*, 2020). The primary feasibility outcomes will be evaluated by assessing recruitment rates (the rate of participants recruited to the study); retention rate (the number of participants who complete measures at baseline and at follow up post intervention) and minimum average attendance (number of participants who attended at least 65% of the intervention sessions). Hence, we aim to recruit a minimum of 72 participants in total (n=12 per cluster) allowing for 20% attrition (n=60; n=10 per cluster), we will be able to estimate a recruitment rate of 60% within a 95% confidence interval +/- 12.6%; a retention rate of 80% within a 95% confidence interval of +/- 10.3% and a minimum average attendance of 65% within a 95% confidence interval of +/- 12.3%. 

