Recruitment rates: will be assessed by reporting the recruitment rate (as the number of participants recruited and randomised per centre per month and the number of people enrolled over the number of people who expressed an interest in taking part). Refusal rates will also be documented where provided.Retention: proportion of individuals who after enrolment completed the baseline and follow-up assessments. We will record numbers who completed baseline and assessment at 12-week follow-up and attendance at programme. We will calculate the minimum outcome assessment target, which is set at a retention rate of at least 80% of recruited participants with valid baseline and 12-week primary outcome data i.e., less than 20% attrition at outcome assessments at baseline and follow-up.Attendance at supervised sessions: We will record the percentage of participants that attend the supervised sessions (adherence). Minimum average attendance target will be determined as the minimum average attendance by recruited participants set as 65%.Participation in home exercise programme: Using a self-complete calendar we will record how many participants (and how often) they engage in the home exercise programme.Safety will be assessed through self-report of direct or unrelated adverse events (e.g., falls or pain during the programme period). Falls: A falls diary (Appendix 7) will be completed. Participants or a nominated family member/career will receive a weekly reminder to complete the log. Completing a falls diary encourages recall, identifies the key circumstances surrounding falls and their content focuses the programme. The falls diary will include: Date and time of fall; location of fall; what caused the fall; type of injury sustained; and action taken. The falls diary is more accurate than retrospective recall over varying time periods.

The variability, consistency, response rates and data completeness for each of the secondary outcome measures will be determined. The secondary outcomes of the study have been used in previous studies with older adults, have undergone psychometric testing and include:

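### The primary recruitment rate is defined differently across sections, its stated ±12.6% uses the denominator of neither definition, and no numeric recruitment criterion is declared

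*Protocol article*

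**What the plan says.** The protocol article describes the recruitment outcome in four places.

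- **Abstract, Outcomes:** it is "the number of participants recruited per cluster per month", a count per unit of time.
- **Sample size:** the outcome is given as "recruitment rates (the rate of participants recruited to the study", with no denominator. The section then promises to estimate "a recruitment rate of 60% within a 95% confidence interval +/- 12.6" percentage points, so here it is treated as a proportion. Beside it stand "a retention rate of 80% within a 95% confidence interval of +/- 10.3" points and 65% attendance within 12.3 points.
- **Assessment procedures, feasibility list:** two measures are joined by *and*. One is the number recruited and randomised per centre per month. The other is "the number of people enrolled over the number of people who expressed an interest in taking part". Neither is marked as primary.
- **Table 1, primary aim, criterion for feasibility:** "The rate of participants recruited to the study", with no value.

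Assessment procedures sets targets for retention (at least 80%) and for average attendance (65%). It sets none for recruitment. The Process evaluation section will ask whether recruitment was sufficient, without saying what that means. The only recruitment numbers are in Sample size: a minimum of 72 participants (12 per cluster), and the 60% used for precision.

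**The concern.** A count per cluster per month cannot equal 60%, so the Abstract and the Sample size section do not describe the same quantity. A precision statement is meaningful only for a named numerator and denominator, and here the reader cannot tell which measure the 12.6 points belong to.

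The article makes a definitive trial conditional on evidence of feasibility, and recruitment is the first element of that. If neither the primary measure nor its criterion is fixed, the judgement that recruitment was adequate will be made after the numbers are known. The planners of the next trial would also inherit a precision figure that does not describe the data collected.

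**Working it through.** **Inputs.** From Sample size: 72 recruited, 20% attrition, 60 stated as remaining; planning values 60%, 80% and 65%; half-widths 12.6, 10.3 and 12.3 points. From Assessment procedures: the proportion is enrolled divided by those who expressed interest.

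**1. Reproduce the plan's figures.** Half-width = 1.96 × √(p(1−p)/n), with no allowance for clustering.

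| n | p = 0.60 | p = 0.80 | p = 0.65 |
|---|---|---|---|
| 58 | 12.61 | 10.29 | 12.28 |
| 60 | 12.40 | 10.12 | 12.07 |
| 72 | 11.32 | 9.24 | 11.02 |
| Stated | 12.6 | 10.3 | 12.3 |

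Only n = 58 matches all three. Solving n = 1.96² p(1−p)/h² for each stated half-width h gives 58.1, 57.9 and 57.8. This is 72 × 0.8 = 57.6 rounded up, the number expected to complete. The 60 printed in the section is 83.3% of 72, not 80%, and does not reproduce the figures by this formula. A t quantile with n = 60 gives 12.66, 10.33 and 12.32, which matches only if the decimals are cut off rather than rounded. On either route the denominator is the retained sample.

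**2. Is that a denominator for recruitment?** If 60% were taken of 58 people, 0.60 × 58 = 34.8, so about 35 would be enrolled, not 72. Completers are counted after recruitment and cannot be the base for it.

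**3. The proportion as Assessment procedures defines it.** With 72 enrolled at 60%, those who expressed interest number 72/0.60 = 120. The half-width is 1.96 × √(0.60 × 0.40/120) = 0.0877, or 8.8 points.

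The number who will express interest is not stated, so with 72 enrolled:

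| Expressed interest | Proportion enrolled | Half-width (points) |
|---|---|---|
| 90 | 80% | 8.3 |
| 120 | 60% | 8.8 |
| 180 | 40% | 7.2 |
| 240 | 30% | 5.8 |

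The largest possible value comes at a proportion of 2/3 (72/108): 1.96 × √(0.667 × 0.333/108) = 8.9 points. With 72 enrolled, this formula therefore never gives 12.6.

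**4. The monthly count.** A half-width in percentage points does not apply. If 72 is treated as a Poisson count with no variation between clusters, the exact 95% interval is 56.3 to 90.7. That is 56.3/72 = 0.78 to 90.7/72 = 1.26, or about −22% to +26%. The absolute rate depends on the recruitment period, which the article does not give. If it were 2, 3 or 6 months, 12 per cluster would be 6, 4 or 2 per cluster per month.

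**5. Criterion.** For retention, both Assessment procedures and Table 1 give a number. For average attendance, Assessment procedures gives one. For recruitment, neither does.

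**The case against.** The strongest reply is that Assessment procedures is the operative definition and commits to reporting both measures, with refusals where available. A proportion is thus a named outcome, the two measures complement each other, and neither can be dropped unseen. This stands. A reader might infer that the investigators are free to report whichever measure looks better, and the article does not support that. What is open is which measure is primary and which one the Sample size section and Table 1 mean.

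A reader might also infer that recruitment cannot fail. That goes too far. Sample size sets a minimum of 72, with 12 per cluster, and says that a group below 10 to 12 is hard to sustain, so a shortfall would be visible. But neither 72 nor 60% is called a feasibility criterion.

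Nor is Table 1 a clean contrast between recruitment and the other two outcomes. Its 65% is the share of sessions a participant must attend. The average-attendance target is in Assessment procedures, so only retention has a true threshold in the table.

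The stated 12.6 points is wider than 8.8, so the error is on the cautious side. That also stands, and no claim of inadequate precision is made here.

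Finally, progression rules may sit in a fuller protocol or an analysis plan. This weakens the point about the missing criterion, although Table 1 has a column for it and the recruitment entry holds no value. It does not touch the conflicting definitions or the denominator.

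**Conclusion.** The point holds in three parts.

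1. The primary recruitment outcome is a monthly count in the Abstract, an unlabelled rate sized as a proportion in Sample size, both kinds of measure in Assessment procedures, and an unlabelled rate in Table 1.
2. The 12.6 points rest on about 58 expected completers, the denominator of neither recruitment measure. For the defined proportion the figure is about 8.8 points, and for the monthly count it does not apply.
3. The article declares no recruitment pass/fail criterion.

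The 8.8 assumes exactly 72 enrolled at the plan's own 60%, and independent individuals, as the plan's own calculation does. Willingness to join may vary between regions and would widen it. A design effect of 120/58 = 2.07 would bring it back to about 12.6, but Sample size mentions none, and the match of all three figures at one n shows that none was used.

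One might read 60% as the intended threshold because it stands beside 80% and 65%, which are targets elsewhere. The article uses it only as a planning value, so that is for the investigators to confirm. The consequence is for the clarity of the feasibility decision, not for the sample size.

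**What to change.** - Name one primary recruitment measure, with numerator and denominator, and use the same words in the Abstract, Sample size and Table 1. Enrolled over those who expressed interest is the measure already in Assessment procedures that is compatible with a 60% planning value. Keep the other as descriptive. If the monthly count is preferred as primary, the 60% and its interval should be replaced by a precision statement for a count.
- Replace the 12.6 points with the precision for the chosen denominator: about 8.8 points if 72 of about 120, with the assumed number expressing interest stated.
- Enter a numeric recruitment criterion in Table 1. The investigators should state whether 60% is meant as that criterion and, if not, give the value that is.

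The cost is wording in three places and one recalculated figure. No new data are needed: interested people contact the research team under Screening, and Assessment procedures already requires them to be counted. As the article reports the study as ongoing, the clarification should be dated and made before recruitment results are summarised.
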